## Methods/Design

### Sample size calculation

The main outcome of this study will be any caries increment or not (change in decayed, missing, and filled teeth (△dmft >0 or = 0) in the study children. Our latest survey showed that about 35% of Hong Kong children aged 3 years develop new caries in one or more teeth (△dmft >0) in a year [24]. An intervention will be considered to have a clinically significant effect if it reduces this rate to 20% in a year. Such a magnitude of effect size (relative risk of 0.57) was also reported by a previous MI trial in infants [15]. In order to detect such a reduction at a significance level of 5% and a statistical power of 80%, 184 parent-child dyads per group will be needed (multiple comparisons considered). Allowing for a 20% attrition rate, 230 parent-child dyads would need to be recruited into each of the three study groups. The total sample size will be 690.

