A research nurse will review the screening questionnaire and recruit all eligible parent-child dyads who agree to participate. After baseline data collection, participants in each kindergarten will be randomly assigned into three groups (1, CE; 2, CE + MI; and 3, CE + MI + RA) by a research assistant not involved in the enrolment of the participants, delivery of intervention, or data collection. The randomization will be stratified by parental education (“secondary education or below” or “tertiary education”) and child’s caries experience at baseline (“dmft = 0” or “dmft >0”), which are perceived important confounders in this study. For each stratum, to ensure an equal number of subjects in each group (that is, an allocation ratio 1:1:1), a block randomization will be performed (block size of 6). A computerized random sequence generator will determine intervention status of the subjects. Intervention status is then placed into a sequentially numbered envelope for each group and each envelope is sealed and opened before the delivery of intervention so that allocation concealment can be achieved.

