### Training counselors

Two dental hygienists will be trained to deliver counseling to the second group (CE + MI) and third group (CE + MI + RA). Training materials have been prepared by referring to key MI literature and guide books [17,18], a dental MI workbook [27], and the interactive RA program (Cariogram) manual [23]. The training will be delivered by an expert panel composed of a health psychologist experienced in MI counseling and two public health workers specialized in dental interventions and caries risk assessment. The 12-hour training will be customized to involve key caries-related behaviors and typical scenarios commonly encountered in the dental settings. Training sessions will include lectures, discussions, demonstrations, and role plays. A hygienist will proceed to contact subjects only after demonstrating satisfactory competency as assessed by the panel using the Motivational Interviewing Treatment Integrity (MITI) Coding System [28] and a skill evaluation scheme on using Carigoram.

In each of the two groups (CE + MI and CE + MI + RA), participants will be randomly divided into two halves, who will be interviewed by the two counselors, respectively. To ensure the counseling is being delivered consistently with high fidelity to the MI principles, all counseling sessions will be audio-recorded and 20% of randomly selected sessions will be continuously reviewed and rated using the MITI coding system.

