### Statistical analysis

Participants in the three intervention groups will be compared on their demographic background (age and gender), family socioeconomic status (parental education and family income), and baseline oral health behaviors and tooth status. The effectiveness of the intervention schemes will be evaluated and compared over 12 and 24 months through an intention-to-treat analysis, in which participants will remain in their originally assigned group regardless of the intervention actually received and subsequent withdrawal or deviation from the original intervention protocol [31]. For those who are lost to follow-up, the last assessment made will be considered valid throughout the study period.

The primary outcome will be caries increment in children and the proportion of caries-free children, measured by the number of new carious teeth (△dmft; continuous variable) and whether there are any new carious teeth (△dmft >0 or = 0; dichotomous variable). Secondary outcomes will be changes in parental efficacy in protecting children’s oral health and changes in children’s dental behaviors (outcome variables described in Table 2). Effect sizes (relative risk) and their confidence intervals will be calculated. Chi-square tests will be used for comparing proportions; means will be compared through parametric or non-parametric methods, as appropriate. Number needed to treat, calculated as 100 divided by the risk difference expressed as a percentage [32], will be presented to provide an estimate of the number of parents needed to be counseled in order to avoid one child with new dental caries.

**Table 2 T2:** Outcome variables

**Outcomes**	**Variables**	**Codes**	**Source of information**

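### Randomisation is stratified by parental education and baseline caries, but the named chi-square test for the main outcome ignores both, which gives up some efficiency if the strata are prognostic

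*Protocol article*

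**What the plan says.** **Design (Recruitment and randomization).** After baseline data collection, participants in each kindergarten are allocated 1:1:1 in permuted blocks of 6. "The randomization will be stratified by parental education" (two levels) and by the child's baseline caries experience (dmft = 0 or >0), "which are perceived important confounders in this study". Kindergarten is not listed as a stratification factor, but allocation is made inside each one, and 12 are planned.

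**Analysis (Statistical analysis).** For all outcomes, including the dichotomous main outcome (any new carious teeth), the tests named are: "Chi-square tests will be used for comparing proportions; means will be compared through parametric or non-parametric methods, as appropriate". Relative risks with confidence intervals and the number needed to treat are also promised. No stratum, covariate or kindergarten term is mentioned.

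**Sample size (Sample size calculation).** The assumed control rate is "about 35% of Hong Kong children aged 3 years develop new caries in one or more teeth" in a year. The target is stated as "An intervention will be considered to have a clinically significant effect if it reduces this rate to 20% in a year". With 5% significance and 80% power, "184 parent-child dyads per group will be needed (multiple comparisons considered"). The multiplicity method is not named.

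**The concern.** The design and the named test do not match. Stratified blocking removes most of the chance imbalance between arms in the stratification factors. The true sampling variance of the difference in proportions then no longer contains the between-stratum part. An ordinary chi-square test still counts that part in its variance, so its standard error is too large whenever the strata predict the outcome. The protocol itself regards them as important.

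At stake are a test that rejects less often than its nominal level, confidence intervals that are wider than they need be, and power that could be had from data already collected before randomisation. The direction of the error is conservative.

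**Working it through.** **1. Reproduce the planned sample size.** Inputs from Sample size calculation: p1 = 0.35, p2 = 0.20, power 80%, overall significance 5% (taken as two-sided). Pooled two-proportion formula:

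n = [z(α/2)·√(2·p̄·q̄) + z(β)·√(p1·q1 + p2·q2)]² / (p1 − p2)²

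Here p̄ = 0.275, so 2·p̄·q̄ = 0.39875, and p1·q1 + p2·q2 = 0.2275 + 0.16 = 0.3875.

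- No multiplicity correction, z = 1.960: n = 137.9, so 138.
- Bonferroni for three pairs, α = 0.05/3 = 1.67%, z = 2.394: n = (2.394 × 0.6315 + 0.8416 × 0.6225)² / 0.0225 = 184.2, so 185.
- Šidák for three pairs, z = 2.388: n = 183.5, so 184.

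The stated 184 therefore reproduces as an unadjusted two-proportion comparison with three pairwise tests. Power at 184 per arm and α = 0.05/3 is 80.0%. Attrition: 184/0.8 = 230 per group, and 3 × 230 = 690.

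**2. Why the standard error is too large.** With arms exactly balanced on a stratum factor, the variance per child in one arm is p(1 − p) − B, where B is the between-stratum variance of risk. The chi-square test uses p(1 − p).

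Illustration for baseline caries alone, assuming 25% prevalence, an odds ratio of 5 and an overall risk of 35%:

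- Stratum risks are 25.6% and 63.2% (0.75 × 0.256 + 0.25 × 0.632 = 0.35).
- B = 0.25 × 0.75 × (0.632 − 0.256)² = 0.0266.
- Standard error ratio = √[0.2275 / (0.2275 − 0.0266)] = 1.064.
- Effective critical value = 2.394 × 1.064 = 2.547, so the actual type I error is about 1.1% instead of 1.67%.

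**3. Simulation with the stated allocation.** 3,000 trials per setting, 184 per arm, 12 kindergartens × education × baseline caries (48 cells), permuted blocks of 6, rates 35% vs 20%, two-sided α = 0.05/3. The chi-square test was compared with Cochran-Mantel-Haenszel (CMH) tests over the four education × caries strata and over all 48 cells.

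Assumptions not in the documents: baseline caries prevalence 25%; tertiary education 40%; education odds ratio 1, 1.3, 1.5, 1.5 and 2, and between-kindergarten SD on the logit scale 0, 0.2, 0.3, 0.3 and 0.5, in the order of the rows.

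| Baseline-caries odds ratio | Type I error, chi-square | Model SE / true SD under null | Power, chi-square | Power, CMH 4 strata | Power, CMH 48 cells |
|---|---|---|---|---|---|
| 1 | 1.9% | 1.00 | 80.2% | 80.2% | 78.6% |
| 2 | 1.7% | 0.99 | 80.2% | 80.8% | 79.7% |
| 3 | 1.2% | 1.05 | 81.1% | 83.0% | 82.1% |
| 5 | 1.0% | 1.05 | 81.1% | 85.1% | 84.1% |
| 8 | 0.8% | 1.09 | 82.9% | 88.4% | 88.2% |

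Monte Carlo error is about 0.7 points on power and 0.2 points on type I error, so the first two rows show no departure from the nominal 1.67%.

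**4. Reading the table.** Power gained by stratifying on the four cells is 0 at an odds ratio of 1, about 0.5 points at 2, 2 at 3, 4 at 5 and 5.5 at 8. Stratifying on all 48 cells gains slightly less, and costs 1 to 2 points when the strata are not prognostic (80.2% to 78.6%).

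**The case against.** The strongest reply is that nothing planned fails. The trial was sized for a simple two-proportion comparison, and the chi-square test delivers the planned 80% in every row above. This stands. A reader might infer from an oversized standard error that the trial is underpowered, or that its error rate is inflated. Neither follows: the power loss is only relative to a better analysis, and the type I error moves down.

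A second reply is that a condensed article may leave adjustment to an analysis plan that is not shown. This stands in part. The wording for means is open enough to include a covariate-adjusted comparison, and the choice of model for the count of new carious teeth is ordinary analysis-plan detail, so neither is a fault here. The chi-square test for proportions, however, is a stated choice.

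A third reply concerns size, and it also stands. The documents give neither the prevalence of baseline caries nor its association with new caries. Larger losses can be produced by assuming stronger associations. For example, stratum risks of 70% vs 12% imply an odds ratio of (0.70/0.30)/(0.12/0.88) = 17. Nothing in the protocol supports a value that high. Balance is also only approximate, with about 690/48 = 14 dyads per cell, blocks of 6 and 20% attrition allowed for.

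Two further inferences should be resisted.

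- In the counseled groups "participants will be randomly divided into two halves", one half for each counselor. That is not a stratification factor, and the text shows no error in leaving it out of the comparison.
- Table 2 also lists caries-free status (dmft = 0 or >0), which looks much more closely tied to the baseline stratum. The Statistical analysis text, however, describes the caries-free proportion through new carious teeth. The documents give no baseline prevalence and do not say in which children that status would be compared, so no larger loss can be established.

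**Conclusion.** The mismatch is real and its direction is certain if the strata are prognostic: the protocol balances the arms on two factors that it calls important, then names a test for the dichotomous main outcome that ignores them. The size is modest and conditional. At 184 per arm and α = 0.05/3, the power given up runs from nothing at a baseline-caries odds ratio of 1 to 5 to 6 points at 8. The type I error falls clearly below nominal only from an odds ratio of about 3. These figures rest on the assumed prevalences, odds ratios and kindergarten variation listed above, none of which the documents supply. This is an inexpensive gain in efficiency that should be taken, not a threat to the trial's validity.

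**What to change.** - **Any new caries (primary).** Name a stratified or covariate-adjusted analysis: for example Mantel-Haenszel over the four education × caries strata, or modified Poisson regression with robust variance. Include baseline dmft stratum and parental education.
- **Kindergarten.** In a regression, enter it as main effects or a random effect. Do not stratify on all 48 cells.
- **Reporting.** Give the adjusted relative risk and the adjusted risk difference with confidence intervals. The number needed to treat can then be taken from the adjusted risk difference.
- **Number of new carious teeth.** Adjust the comparison for the same terms.
- **Supportive analysis.** Keep the unadjusted chi-square test.

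The cost is a change of wording and minor programming. The two stratification factors and kindergarten are known before allocation, and the Trial status section says that recruitment has not started, so the analysis can be fixed before any outcome is seen. If the strata prove not to be prognostic, the loss should be negligible: in the simulation the four-stratum test then had the same 80.2% power as the chi-square test. The regression options were not simulated.

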**PRIMARY OUTCOME**			
**Caries increment in child***			
	Number of new carious teeth (△dmft)	Continuous	Dental examination
	Any new carious teeth (△dmft >0 or = 0)	Dichotomous	Dental examination
**Caries free child**	dmft = 0 or >0	Dichotomous	Dental examination
**SECONDARY OUTCOMES**			
**Change in parental efficacy****			
Diet	View on the statement “I can control my child from frequent snacking even when he/she cries for it.”	(1) Decreased;	Questionnaire
		(2) No change;	
		(3) Increased	
Oral hygiene	View on the statement “I can make sure my child’s teeth are brushed thoroughly twice a day even when I am very busy.”	(1) Decreased;	Questionnaire
		(2) No change;	
		(3) Increased	
**Change in child’s dental behavior**			
Diet	Frequency of snacking per day	(1) Decreased;	Questionnaire
		(2) No change;	
		(3) Increased	
Oral hygiene	Frequency of toothbrushing per day	(1) Decreased;	Questionnaire
		(2) No change;	
		(3) Increased	
	Silness-Löe Plaque Index	Continuous	Dental examination

* dmft refers to decayed, missing, and filled teeth.

**Parental efficacy was measured using five-point Likert scale questions (“strongly agree”, “agree”, “neutral”, “disagree”, and “strongly disagree”).

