### Recruitment and randomization

The protocol of this study has been reviewed by the Institutional Review Board of University of Hong Kong⁄Hospital Authority Hong Kong West Cluster. An ethical approval was obtained (#UW 11-483). This study involves parent-child dyads. Informed written consent will be obtained from each participating parent.

To be eligible to join this study, a child should be (a) enrolled in kindergarten Grade 1 (K1), (b) aged 3 years, and (c) having unfavorable oral health behavior(s) (that is, a child who needs intervention). Unfavorable oral health behaviors are defined as “brush teeth less often than twice a day” and/or “snack three times or more a day”. Each child will be required to join this study together with his/her parent (mother or father) who spends the most time with him/her, so that a parent-child dyad can be recruited. A child will be excluded if (i) he/she has a serious medical condition or (ii) his/her parents are non-Chinese speaking and cannot understand the oral health materials and counseling, which will be in Chinese.

A screening questionnaire will be used to identify participants who fulfil the above-mentioned criteria. According to our latest survey in Hong Kong [24], 60% of children aged 3 years have unfavorable oral health behaviors (24% with insufficient toothbrushing only; 26% with frequent snacking only; and 10% with both). To reach the target number of 690 parent-child dyads (230 dyads in each of the three groups), 1,150 children would need to be screened (1,150 × 60% = 690). Considering an average number of 120 children in K1 of a kindergarten and an estimated response rate of 80% (based on our recent experience), 12 participating kindergartens will need to be recruited (120 × 80% × 12 = 1,152).

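### Four of the five secondary variables keep only the direction of change, so the planned comparison ignores order and starting level and cannot separate maintained good behaviour from persistent poor behaviour

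*Protocol article*

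**What the plan says.** Table 2 of the protocol article lists five secondary variables. Two are parental-efficacy items, and the footnote gives their raw scale: "Parental efficacy was measured using five-point Likert scale questions". Two are child behaviours, "Frequency of snacking per day" and "Frequency of toothbrushing per day". All four carry the same coding: decreased, no change, increased. The fifth, the "Silness-Löe Plaque Index", stays continuous.

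The Statistical analysis section refers to Table 2 for the outcome variables and describes the tests in one sentence: "Chi-square tests will be used for comparing proportions; means will be compared through parametric or non-parametric methods, as appropriate".

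Under Recruitment and randomization, a child is eligible with either unfavourable behaviour: brushing less than twice a day, or snacking three or more times a day. The 60% of 3-year-olds expected to qualify are split as "24% with insufficient toothbrushing only; 26% with frequent snacking only; and 10% with both".

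**The concern.** Five ordered answers and a daily count are collected at baseline and at each follow-up, and Table 2 then keeps only the sign of the difference. A fall from 6 snacks to 5 counts the same as a fall from 3 to 1. A parent who stays at the top of the efficacy scale cannot increase and shares a code with one who stays at the bottom. Because one unfavourable behaviour is enough to enrol, many children start out favourable on the other. If they remain so, they are coded like children who remain unfavourable.

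Parental efficacy and child behaviour are two of the three aims in the Background and are named in the null hypothesis. The Discussion also wants to explore behaviours as mediators of the clinical effect. No variable in Table 2 reports how many children meet the thresholds that the trial itself uses to define favourable behaviour.

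**Working it through.** **The plan's own figure.** No power is stated for secondary outcomes. The per-arm number comes from the primary outcome: 35% against 20%, 80% power, 5% significance, multiple comparisons considered. With a two-sided alpha of 0.05/3 (z = 2.394) and a mean proportion of 0.275:

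n = [2.394 × √(2 × 0.275 × 0.725) + 0.842 × √(0.35 × 0.65 + 0.20 × 0.80)]² / 0.15² ≈ 184

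Rounded up this is 185, against 184 stated. Then 184 / 0.80 = 230 recruited per arm. The figure reproduces, and 184 is used below as the number analysed.

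**Who is already favourable.** If enrolled children follow the survey mix, those with frequent snacking only already brush at least twice a day: 26/60 = 43%. Those with insufficient brushing only already snack fewer than three times: 24/60 = 40%. The remaining 10/60 = 17% are unfavourable on both.

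**Power model.** The documents give no effect size, spread or correlation for these outcomes, so the following are assumptions. The latent baseline is standard normal. Follow-up equals ρ × baseline + √(1 − ρ²) × error, plus a 0.3 SD shift in the favourable direction in the treated arm, with ρ from 0.3 to 0.7. Both are cut into ordered levels. The snacking and brushing cut-points match the 40% and 43% above.

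Pairwise power with 184 per arm and alpha 0.05/3, at ρ = 0.5 (range over 0.3 to 0.7):

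| Variable | Chi-square, 3 codes | Ordered test, 3 codes | Raw change | Raw follow-up adjusted for baseline |
|---|---|---|---|---|
| Snacking | 41% (29-67) | 53% (38-78) | 62% (48-84) | 78% (70-91) |
| Brushing | 36% (26-49) | 46% (35-61) | 49% (38-62) | 66% (60-74) |
| Efficacy item | 40% (28-64) | 51% (38-75) | 59% (45-80) | 75% (68-89) |

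For 80% power at ρ = 0.5, the three-code chi-square needs 386 per arm against 194 for snacking, 441 against 245 for brushing and 398 against 203 for efficacy. The ratios are 2.0, 1.8 and 2.0. At alpha 0.05, over the same range of ρ, the chi-square gives about 42-80% and the adjusted raw value about 77-96%.

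**Where the gap comes from.** Take a five-level item with cut-points at 10/30/60/85%, alpha 0.05 and ρ = 0.5:

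- chi-square on three codes: 59%
- rank test on the same codes: 69%, so using order adds 10 points
- the same codes adjusted for baseline: 79%, so baseline adds 10 points
- raw follow-up adjusted for baseline: 87%, so not collapsing adds 8 points

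Thus 20 of the 28 points come from order and baseline. For brushing, which takes few values, the last step is only 77% to 80%. Over the settings examined, collapsing alone, with baseline adjustment held equal, costs about 1 to 14 points.

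**Interpretability.** In the same model, 35-36% of control children coded no change on snacking, and 38-40% on brushing, were already favourable at baseline. The code mixes them with children who stayed unfavourable.

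**The case against.** The strongest reply is that the coding itself does limited damage. With baseline adjustment equal on both sides, collapsing costs a few points to the low teens. A reader comparing only the first and last columns of the table might infer that the three categories alone cost that much power. The decomposition does not support this, and the reply stands.

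The article also does not assign a test to the three-level codes by name. It gives chi-square to proportions and allows non-parametric methods for means, so a rank test on the ordered codes is conceivable and would recover part of the loss. Chi-square is still the only named test that directly fits a categorical code. The coding itself is stated in Table 2 and is not left open.

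Three stronger readings are tempting and unsupported:

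- A reader might infer that no change is scored as failure. Table 2 gives three neutral codes and labels none of them success or failure. A child favourable at baseline can still be coded as increased or decreased, and no enrolled child is favourable on both behaviours.
- A reader might infer bias. Individual 1:1:1 randomisation spreads already-favourable children evenly over the arms in expectation.
- A reader might blame the coding for diluting an effect confined to children with room to improve. That dilution comes from the either/or eligibility rule, and it would remain in a whole-arm share meeting the threshold.

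Finally, the raw values are collected, so the trial could still report threshold attainment. Table 2 simply does not name it as an outcome.

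**Conclusion.** The point holds as an inefficient, hard-to-read definition of four secondary variables. It does not threaten the trial's validity. Under the assumed shift and correlations, the three-code chi-square has about 42-80% power at alpha 0.05, against 77-96% for the raw response adjusted for baseline. Most of the difference is due to ignoring order and starting level. These figures illustrate scale only: they move with the assumed effect, cut-points and correlation, though the direction was the same in every setting tried. The comparator simulated was a linear model with baseline; the ordinal model recommended here was not itself simulated. The 43% and 40% shares rest on the article's survey mix carrying over to those enrolled.

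The Plaque Index, the caries outcomes and the total of 690 are untouched.

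**What to change.** Amend Table 2 and the Statistical analysis section as follows:

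- Analyse the follow-up five-point response and the follow-up daily frequency with an ordinal (proportional-odds) model containing arm, baseline value and the two stratification factors, parental education and baseline caries experience.
- Report the share of children meeting each of the trial's own thresholds at follow-up (brushing at least twice a day; snacking fewer than three times a day), adjusted for baseline status.
- Keep the decreased / no change / increased table as description.

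The cost is wording, slightly more analysis work and a proportional-odds assumption to check. No new data are needed, and the Trial status section says recruitment has not begun, so the change can be made before any outcome is seen.
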